**Surgical Report Form**

Date \_\_\_\_\_

First surgeon's name \_\_\_\_\_

Second surgeon's name if applicable \_\_\_\_\_

Name of Participant \_\_\_\_\_

**The Participant has:**

**Yes No**

- ☐ ☐ Allergy to local anaesthetic
- ☐ ☐ Hemophilia or easy bleeding
- ☐ ☐ Anemia
- ☐ ☐ Currently taking aspirin?

- ☐ ☐ Urethral Discharge
- ☐ ☐ Genital ulcers or warts
- ☐ ☐ Difficulty with sexual function or erections
- ☐ ☐ Painful or difficult urination
- ☐ ☐ Other problem \_\_\_\_\_

**Unicirc 004**

|         |                     |                   |                                             |
|---------|---------------------|-------------------|---------------------------------------------|
| Center: | Participant Number: | Study Staff Name: | Date of Visit:                              |
|         | _ _ _               | _ _ _             | _ _ _ / _ _ _ /2 0 1 _ _ 
Day Month Year |

**Surgical Report Form**

**Genital exam:**

☐ Normal ☐ Abnormal

Specify if abnormal \_\_\_\_\_

**The surgical procedure**

Check box if EMLA cream used ☐

Local anaesthesia: Amount: \_\_\_\_\_ ml ring block, \_\_\_\_\_ ml in frenulum and \_\_\_\_\_ ml additional.

Frenulectomy done: Yes ☐ No ☐

☐ Circumcision with Unicirc and tissue adhesive. Estimated blood loss \_\_\_\_\_ ml.

Size of Unicirc instrument used \_\_\_\_\_

☐ Open surgical circumcision. Estimated blood loss \_\_\_\_\_ ml

**Total time of circumcision (from first surgical incision or placement of Unicirc until start of dressing):**

\_\_\_\_\_ min.

**Notes:**

**Complications:**

**Surgeon's signature:** \_\_\_\_\_

### Post-Operative Instructions Unicirc

Participant ID \_\_\_\_\_

If you have complications or questions, call the Doctor.

Doctor's name and phone contact \_\_\_\_\_

Phone number of Medical Centre \_\_\_\_\_

- Swelling is normal in the first week, but if the wound hurts or swells more or gets redder, call the doctor.

- Take paracetamol, two tablets every 4-6 hours when needed for pain (up to 8 tablets per 24 hours)

The adhesive tape (Hypafix) should remain in place for 7 to 10 days, until it falls off. If it has not fallen off by 2 weeks, wet the area and remove it gently.

How to care for your wound:

- Leave only the tape as a dressing. The tape should stay dry.

- You may wash briefly but do not soak or scrub the area. To dry, rub gently with a soft towel.

- Avoid ointments. Do not apply creams or lotions, creams, Vaseline or any other product to the wound.

- Do not rub, scratch or pick at the wound.

- Redness, swelling and pain are common at first, and should be less every day. Contact us if there is increased redness, swelling or pain, if the wound is hot to the touch, or if the wound edges reopen or separate.

| Follow-up visits   | Date |
|--------------------|------|
| 7 days             |      |
| 4 weeks            |      |
| 6 weeks (optional) |      |

**Protocol, UNICIRC clinical trial 004**  
**Follow-Up Visit: Genital Exam and Wound Healing**

|                |                                        |                                      |                                                                       |
|----------------|----------------------------------------|--------------------------------------|-----------------------------------------------------------------------|
| Center: | Participant Number:
 _ _ _ _ | Study Staff Name:
 _ _ _ _ | Date of Visit:
 _ _ _ / _ _ _ /2 0 1 _ _ 
Day Month Year |
|----------------|----------------------------------------|--------------------------------------|-----------------------------------------------------------------------|

**Follow-up Visit (7 days, maximum 10 days after circumcision)**

**1. Is this a scheduled visit?**..... |\_|\_|

0 = No  
1 = Yes

**1a. If NO, what is the reason for this unscheduled visit?** \_\_\_\_\_  
 \_\_\_\_\_

**2. What is the post-op day?** .....|\_|\_|\_|  
 e.g. 07 = Day 7

**GENITAL EXAM**

**3. Aside from the circumcision wound, are the genitals normal?** ..... |\_|\_|

0 = No  
1 = Yes

**3a. If NO, describe:** \_\_\_\_\_  
 \_\_\_\_\_

**WOUND HEALING**

**4. Did the participant have any difficulty keeping the wound clean and dry?** ..... |\_|\_|

0 = No  
1 = Yes

**5a. If YES, describe:** \_\_\_\_\_  
 \_\_\_\_\_

**5. Is there wound disruption or dehiscence?**..... |\_|\_|

0 = None    1 = < 2cm  
2 = More than 2 cm

**6. Is there any swelling?**..... |\_|\_|

0 = None    2 = Moderate  
1 = Mild    3 = Severe (if severe, report as Adverse Event)

**For Questions 7-11, if response is "moderate" or "severe," complete AE form and take a picture with participant's permission.**

**7. Is there any evidence of infection?**..... |\_|\_|

0 = None    2 = Moderate  
1 = Mild    3 = Severe

**8. Is there any bleeding?**..... |\_|\_|

0 = None    2 = Moderate  
1 = Mild    3 = Severe

**9. Is there a hematoma?**..... |\_|\_|

0 = None    2 = Moderate  
1 = Mild    3 = Severe

**10. Does the participant report difficulty or pain with urination?** ..... |\_|\_|

0 = None    2 = Moderate  
1 = Mild    3 = Severe

**11. Are there any other complications?**..... |\_|\_|

0 = None    2 = Moderate  
1 = Mild    3 = Severe

**13a. If response is 1, 2, or 3, describe complication:** \_\_\_\_\_  
 \_\_\_\_\_

**12. Was any medication given to or prescribed for the participant at this visit?**.....|\_|\_|

0 = No  
1 = Yes → **LIST MEDICATIONS**  
 \_\_\_\_\_  
 \_\_\_\_\_

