**WOUND HEALING**

5. Did the participant have any difficulty keeping the wound clean and dry? .....   
0 = No  
1 = Yes  
**5a. If YES, describe:** \_\_\_\_\_  
\_\_\_\_\_

6. Has the wound completely healed (no wound, completely epithelialized)? .....   
0 = No  
1 = Yes → **SKIP REST OF QUESTIONS**

7. Is there wound disruption or dehiscence?.....   
0 = None    1 = < 2cm  
2 = More than 2 cm

8. Is there any swelling?.....   
0 = None    2 = Moderate  
1 = Mild    3 = Severe (if severe, complete AE form)

For Questions 9-13, if response is "moderate" or "severe," complete AE form and take a photo with participant's permission.

9. Is there any evidence of infection?.....   
0 = None    2 = Moderate  
1 = Mild    3 = Severe

10. Is there any bleeding?.....   
0 = None    2 = Moderate  
1 = Mild    3 = Severe

11. Is there a hematoma?.....   
0 = None    2 = Moderate  
1 = Mild    3 = Severe

12. Does the participant report difficulty or pain with urination? .....   
0 = None    2 = Moderate  
1 = Mild    3 = Severe

13. Are there any other complications?.....   
0 = None    2 = Moderate  
1 = Mild    3 = Severe

**13a. If response is 1, 2, or 3, describe complication:** \_\_\_\_\_  
\_\_\_\_\_

14. Was any medication given to or prescribed for the participant at this visit?.....  
0 = No  
1 = Yes → **LIST MEDICATIONS**  
\_\_\_\_\_  
\_\_\_\_\_

15. Final Cosmetic Result .....  
1= Regular  
2= Irregular  
3 =Scalloped (wavy)

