## UNSCHEDULED VISIT FORM

1. What is the reason for this unscheduled visit?

\_\_\_\_\_

2. What is the post-op day? .....|\_|\_|\_|

3. Aside from the circumcision wound, are the genitals normal? .....|\_|\_|

0 = No  
1 = Yes

3a. If NO, describe: \_\_\_\_\_

\_\_\_\_\_

4. Did the participant have any difficulty keeping the wound clean and dry? .....|\_|\_|

0 = No  
1 = Yes

5a. If YES, describe: \_\_\_\_\_

\_\_\_\_\_

5. Is there wound disruption or dehiscence? .....|\_|\_|

0 = None 1 = < 2cm  
2 = More than 2 cm

6. Is there any swelling? .....|\_|\_|

0 = None 2 = Moderate  
1 = Mild 3 = Severe (if severe, report as Adverse Event)

**For Questions 7-12, if response is "moderate" or "severe," complete AE form and take a picture with participant's permission.**

7. Is there evidence of infection? .....|\_|\_|

0 = None 2 = Moderate  
1 = Mild 3 = Severe

8. Is there bleeding? .....|\_|\_|

0 = None 2 = Moderate  
1 = Mild 3 = Severe

9.

Is there a hematoma? .....|\_|\_|

0 = None 2 = Moderate  
1 = Mild 3 = Severe

10. Does the participant report difficulty or pain with urination? .....|\_|\_|

0 = None 2 = Moderate  
1 = Mild 3 = Severe

11. Are there any other complications? .....|\_|\_|

0 = None 2 = Moderate  
1 = Mild 3 = Severe

13a. If response is 1, 2, or 3, describe complication: \_\_\_\_\_

\_\_\_\_\_

12. Was any medication given to or prescribed for the participant at this visit? .....|\_|\_|

0 = No  
1 = Yes → LIST MEDICATIONS

\_\_\_\_\_

\_\_\_\_\_

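### No visit form attaches an adverse-event instruction to wound dehiscence, even above 2 cm, and complications that resolve between visits have no structured record

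*Protocol*

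**What the plan says.** Three forms in the protocol collect complications after the procedure: the 7-day follow-up form, the 4-week and optional 6-week form, and the unscheduled visit form. Each asks "Is there wound disruption or dehiscence" and codes the answer as none, under 2 cm, or "2 = More than 2 cm". No AE instruction stands beside that item on any form.

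The swelling item comes next and carries its own instruction, on the 7-day form "3 = Severe (if severe, report as Adverse Event".

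The general rule follows. On the 7-day form it reads "For Questions 7-11, if response is 'moderate' or 'severe,' complete AE form", and it also asks for a photograph if the man agrees. The 4/6-week form begins its rule "For Questions 9-13, if response is" and the unscheduled form "For Questions 7-12, if response is". Each range ends with, or takes in, a catch-all item, "Are there any other complications", graded none to severe.

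On the 4/6-week form, a yes to complete healing (Q6) tells staff to skip the remaining questions. Dehiscence (Q7) and every item in the AE range (Q9 to Q13) come after that point.

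The Summary lists operative and post-operative complications as a secondary outcome. It does not say which form they are counted from.

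**The concern.** The Unicirc arm is sealed with tissue adhesive and compared with open surgical circumcision, so separation of the wound edges bears directly on how the new method closes the wound. The protocol expects such events. The Unicirc post-operative sheet asks men to make contact if the edges come apart, and the AE form asks whether extra sutures were needed and how many were placed. Yet the visit forms contain no instruction that leads from a large opening to that AE form.

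At stake is the completeness and evenness of the safety comparison. If AE reporting of dehiscence is left to individual staff, some openings will have a photograph and a treatment record and others will not, with no rule to make this equal between arms. The Summary expects the trial to show that the method is safer, and a count that depends on who filled in the form is a weak basis for that.

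A second gap concerns timing. The items ask what is present on the day of the visit. A complication that arose and settled between visits can correctly be answered as none, or not be asked about at all.

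**Working it through.** No figure in the protocol bears on this point, so the check sets the forms side by side.

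**Step 1. Item number against AE range**

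| Form | Dehiscence item | AE range | Inside? | Own AE instruction for dehiscence | Own AE instruction for swelling |
|---|---|---|---|---|---|
| 7-day | Q5 | Q7–11 | No | None | Yes, if severe (Q6) |
| 4/6-week | Q7 | Q9–13 | No | None | Yes, if severe (Q8) |
| Unscheduled | Q5 | Q7–12 | No | None | Yes, if severe (Q6) |

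No form of the three has an AE instruction specific to dehiscence. All three record dehiscence with its size.

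**Step 2. Would widening the range repair it?** No. The rule acts on the grades moderate and severe, and the dehiscence codes are lengths. The item needs its own instruction. The length codes also leave an opening of exactly 2 cm without a category.

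**Step 3. Is there another route?** Yes, the other-complications item: Q11 on the 7-day and unscheduled forms, Q13 on the 4/6-week form. A moderate or severe answer there calls for an AE form. Staff would have to enter the same event a second time, under a heading that reads as covering what has not yet been asked, and choose a grade that no rule links to length.

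**Step 4. Timing.** The 7-day visit may take place up to day 10, and the next scheduled visit is at day 28. The interval is 28 − 7 = 21 days, or 28 − 10 = 18 days at the latest. For a man healed at 4 weeks the form asks nothing about dehiscence, infection, bleeding, haematoma or other complications, so the route in Step 3 is closed too. An event that arose and resolved in that interval has a structured record only if he made an unscheduled visit.

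**Step 5. Scale.** The protocol gives no expected dehiscence rate, so the number of affected cases cannot be estimated. On the assumption, which the protocol does not state, that complications are counted from AE forms alone, each uncounted case lowers the observed rate by

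- Unicirc arm: 1/50 = 2.0 percentage points
- Open surgery arm: 1/25 = 4.0 percentage points

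**The case against.** A reader might infer that dehiscence never reaches an AE form and is left out of the complication count. The document does not support either inference.

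- The other-complications item lies inside every AE range, so a route exists, although it rests on judgement.
- Dehiscence is recorded by size on all three forms, so it can be tabulated by arm whether or not an AE form was opened.
- The complications outcome is not defined as events on AE forms. The counting rule may stand in a statistical analysis plan that is not shown, and its absence from the protocol is no fault.
- The AE form is incomplete in the text available, passing from item 1 through a line for listing other entries to item 9. It cannot be said that dehiscence is absent from its event types.

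All of this stands, and it limits the claim to the missing instruction and what follows from it. It does not remove the point. An analysis plan can decide how to count what was recorded, but it cannot recover a photograph, a treatment record or a between-visit event that was never collected.

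On timing, the unscheduled form, the free-text comment fields and the Unicirc advice to make contact are partial safeguards. They depend on the man returning or on staff volunteering a note.

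The unscheduled form's range also takes in Q12, a yes/no medication item. A moderate or severe answer is impossible there, so the slip has no effect.

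**Conclusion.** The concern holds in limited form. On all three forms dehiscence lies outside the AE range, has no instruction of its own although swelling does, and is coded in a way the general rule cannot use. AE reporting of an opening above 2 cm therefore depends on staff re-entering it as another complication. Loss from the complication count is a risk and is not shown. The 2.0 and 4.0 points per missed case apply only if AE forms are the sole source of the count.

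The timing gap holds as written: present-tense items, together with the skip for healed wounds at 4 weeks, leave up to 21 days in which a resolved event has no structured record without an unscheduled visit.

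The primary outcome, intraoperative time, is untouched, and dehiscence present at a visit is still recorded. This is a worthwhile correction to the ascertainment of a secondary safety outcome. It is not a condition for the trial to be valid.

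**What to change.** 1. On all three forms, attach an explicit instruction to the dehiscence item to complete an AE form at its upper category, as is already done for severe swelling.
2. Redraw the length categories so that exactly 2 cm falls in one of them, for example under 2 cm and 2 cm or more.
3. Ask the complication items, including dehiscence, for the period since the last visit. On the 4/6-week form place them before the question on complete healing. If they stay after the skip, the new wording will not reach healed men, whose events are the ones most likely to have resolved.
4. State that dehiscence recorded on the visit forms counts in the complications outcome, whether or not an AE form was completed.

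Correcting the unscheduled form's range to Q7–11 is tidying only.

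The cost is form wording, a few more AE forms, slightly longer 4-week visits for healed men, and possibly a less favourable complication rate. Sample size, visit schedule and primary analysis do not change.

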**SUMMARY**

According to the Framework for Clinical Evaluation of Devices for Adult Male Circumcision (WHO, 2011): *“WHO and other health authorities wish to identify one or more devices that (a) would make the VMMC safer, easier, and quicker; (b) would have more rapid healing than current methods and/or might entail less risk of HIV transmission in the post-operative period; (c) could be performed safely by health-care providers with a minimal level of training; and (d) would be cost-effective compared to standard surgical methods for male circumcision scale up.”*

Because of difficulties and small risks entailed in using sterilizable instruments, WHO prefers disposable, single-use-only instruments be used for circumcision. This proposed randomized controlled trial will provide important data which will inform and enable the South African health system to more effectively scale-up circumcision services. This study will prove that VMMC using the Unicirc disposable single-use-only instrument coupled with tissue adhesive meets WHO criteria for the ideal method: it is faster, easier to learn, safer for both surgeons and patients, heals sooner, has excellent cosmetic results, and is more cost effective than any other currently available technique.

We propose a randomized controlled trial (RCT) comparing this minimally-invasive circumcision technique to the open surgical technique. In accordance with WHO recommendations concerning sample size found in the Framework for Clinical Evaluation of Devices for Adult Male Circumcision, we propose to study:

- Unicirc disposable instrument with topical anaesthetic and tissue adhesive wound sealing: 50 men
- Open surgical circumcision: 25 men

This is the fourth study of Unicirc circumcision, and the second study that uses topical anaesthetic instead of injectable local anaesthetic. Tissue adhesive is widely used in multiple areas of medicine; specifically, multiple observational studies and RCTs have shown cyanoacrylate tissue adhesives to be superior to suture closure in VMMC. The open surgical method will serve as the control intervention.

*Population:* Men at least 18 years of age who desire male circumcision

*Study design:* Randomized controlled trial

*Intervention:* Unicirc instrument circumcision plus tissue adhesive vs. open surgical circumcision

*Follow-up visits:* 7 days and 28 days. Optional 42 day follow-up if not completely healed by 4 weeks.

*Primary outcome:* Intraoperative time

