*Secondary outcomes:* Complications (operative and post-operative); time to healing; direct costs; post-operative pain; patient satisfaction; cosmetic result.

Protocol, UNICIRC clinical trial 004

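### The scheduled follow-up forms never ask what complications occurred since surgery or the last visit, so events that resolved between visits may be missed

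*Protocol*

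**What the plan says.** The protocol Summary lists the secondary outcomes as "Complications (operative and post-operative); time to healing; direct costs; post-operative pain; patient satisfaction; cosmetic result". It plans 50 men in the Unicirc arm ("Unicirc disposable instrument with topical anaesthetic and tissue adhesive wound sealing: 50 men") and 25 in the control arm ("Open surgical circumcision: 25 men"). Follow-up is at "7 days and 28 days. Optional 42 day follow-up if not completely healed by 4 weeks". The first form carries the window "Follow-up Visit (7 days, maximum 10 days after circumcision").

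Under Wound Healing on the 7-day form, the items on dehiscence, swelling, infection, bleeding and hematoma are all in the present tense, for example "8. Is there any bleeding". The 4-/6-week form repeats them with other numbers, for example "9. Is there any evidence of infection". Two further items, on urination and on other complications, are also in the present tense but state no recall period.

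On both forms an adverse event form is required for severe swelling, and for a moderate or severe answer on infection, bleeding, hematoma, urination or other complications. Dehiscence has no such trigger.

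On the 4-/6-week form, item 6 asks whether the wound has healed completely. A yes sends the examiner past all remaining questions, including complication items 7 to 13.

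**The concern.** A complication rate is normally read as the proportion of men who had an event at any time from surgery to the end of follow-up. A present-tense question at an examination yields something narrower: the proportion with the condition on that day. The two agree only if events last until the next visit or reach the record by another route.

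Bleeding, hematoma and infection can begin and end within days. A bleed on day 2 that has stopped by day 7 is properly coded as none, and that answer prompts no adverse event form. An infection on day 12 that was treated elsewhere and has cleared by day 28 gets no prompt at all if the wound is healed by then.

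The Summary expects the study to show that the technique is safer. Small event counts in 50 and 25 men would inform that statement, and an analysis plan cannot restore events that the forms never elicited.

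**Working it through.** The protocol states no complication rate, power or error figure for this outcome, so there is none to reproduce. The check is mainly a reading of the forms.

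**Step 1: what each scheduled item covers**

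| Item | 7-day form | 4-/6-week form | Look-back wording | Adverse event trigger |
|---|---|---|---|---|
| Dehiscence | 5 | 7 | none | none |
| Swelling | 6 | 8 | none | severe only |
| Infection | 7 | 9 | none | moderate or severe |
| Bleeding | 8 | 10 | none | moderate or severe |
| Hematoma | 9 | 11 | none | moderate or severe |
| Urination (participant-reported) | 10 | 12 | none; recall period unstated | moderate or severe |
| Other complications (open) | 11 | 13 | none; recall period unstated | moderate or severe |

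The question on keeping the wound clean and dry is in the past tense, but it concerns wound care. The medication question is confined to the visit itself, so treatment received elsewhere has no field there.

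**Step 2: unobserved intervals**

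- Surgery to first visit: 7 days, at most 10.
- First to second visit: 28 − 7 = 21 days, or 28 − 10 = 18 if the first visit is late.
- Second to optional visit: 42 − 28 = 14 days, only for men not yet healed.

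**Step 3: effect of the skip**

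A man healed at day 28 answers none of items 7 to 13. For him those items are unanswered, not answered as none. No scheduled question covers complications in the 18 to 21 days since his first visit. This follows from the form and needs no assumption.

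**Step 4: other routes**

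- The Surgical Report Form has a complications field, for operative events.
- The Unscheduled Visit Form repeats the items and records the post-operative day. The scheduled forms can also be marked as unscheduled.
- The Unicirc instruction sheet asks men to call about complications.
- Comments fields and the adverse event form can take an event that someone mentions.

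After the operation, all of these depend on the man returning, calling or volunteering the event.

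**Step 5: illustration of size**

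Assumptions, none from the document: true proportion of men with an event p = 4%, 10% or 20%; share missed m = 0 to 75%, the same in both arms. The recorded rate is q = p(1 − m), the expected count n·q, and the chance of recording no event (1 − q)^n.

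| p | m | Expected, n = 50 | Expected, n = 25 | P(none), n = 50 | P(none), n = 25 |
|---|---|---|---|---|---|
| 4% | 0 | 2.0 | 1.0 | 13.0% | 36.0% |
| 4% | 50% | 1.0 | 0.5 | 36.4% | 60.3% |
| 10% | 0 | 5.0 | 2.5 | 0.5% | 7.2% |
| 10% | 25% | 3.75 | 1.88 | 2.0% | 14.2% |
| 10% | 50% | 2.5 | 1.25 | 7.7% | 27.7% |
| 10% | 75% | 1.25 | 0.62 | 28.2% | 53.1% |
| 20% | 0 | 10.0 | 5.0 | <0.1% | 0.4% |
| 20% | 50% | 5.0 | 2.5 | 0.5% | 7.2% |

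Worked line: p = 10%, m = 50% gives q = 0.05, expected count 50 × 0.05 = 2.5, and 0.95^50 = 0.077.

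As a single realised example, recording 2/50 instead of 5/50 (three of five events lost, m = 60%) moves the exact 95% interval from 3.3–21.8% to 0.5–13.7%.

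With a common m the expected rate ratio between arms is unchanged, because (1 − m) cancels, and the rate difference shrinks by the factor (1 − m). Only unequal shares would distort the ratio.

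**The case against.** The strongest reply is that the forms do not exclude interval events. No item limits itself to the day of examination. The urination item takes the man's own report, and the open item on other complications has free text, so a day-2 bleed that he mentions can be entered there or under Comments. The Unscheduled Visit Form captures any event for which he returns. The stated triggers say when an adverse event form must be completed, not that it may be completed only then. That form is only partly legible in the public text, so onset dates or retrospective reporting may be among its missing items. Complications are also secondary; the primary outcome is intraoperative time.

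Most of this stands, and it rules out several stronger readings. A reader might infer that every item asks only about the visit day; two items leave the recall period open. A reader might infer that interval events are not recorded; those presented or volunteered can be. A reader might infer that the safety conclusion rests wholly on these items; operative complications and unscheduled visits also feed it.

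What the reply does not remove is that every route for an event already resolved by the scheduled visit is passive. It also leaves the healed skip untouched, and that is the firmest textual point.

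**Conclusion.** The concern holds as a risk of under-recording in a named secondary outcome. It rests on three facts on the face of the forms: no complication item asks explicitly about the interval, the physical-sign items describe the state at the visit, and healed men at 4/6 weeks are asked no complication item. Events at risk are those that resolved between visits and were neither presented nor volunteered.

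The direction of this mechanism is downward; its size is unknown. The document gives no complication rate, no time to resolution and no share of men expected to return with a problem, so the tabulated figures show sensitivity and are not estimates. It would go too far to say that the rate has been shown to be undercounted. A bias between arms is also unsupported: it would need different missed shares in the two arms, and nothing in the document establishes that.

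The change should be made because one or two lost events matter in arms of 50 and 25 men, and because the loss cannot be repaired at analysis. The primary outcome is unaffected.

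**What to change.** Revise both scheduled forms as follows.

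1. For dehiscence, swelling, infection, bleeding, hematoma, urination and other complications, record two answers: the worst grade since the operation (7-day form) or since the last visit (4-/6-week form), with onset day and whether treated at the study clinic or elsewhere; and whether it is present today.
2. Place the look-back answers before the healed question and its skip. If they are added to items 7 to 13 where these now stand, healed men will still not be asked.
3. Key the adverse event form to the look-back grade. Because dehiscence is recorded by length and now has no trigger, the sponsor should state whether and how it triggers the form.
4. Define the complication outcome as any event from surgery to the last visit, counted per man and reported by arm.

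The cost is a form revision and about a minute per visit. Recall over about three weeks will bring some error, and the recorded complication rate may be higher and so less favourable. Recall error is a smaller problem than not asking.
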